The primary outcome will be the score obtained by the residents on evaluation questionnaires for each clinical practice guideline. Other included variables will be the sociodemographic and training variables of the residents and the teaching unit characteristics. The statistical analysis will consist of a descriptive analysis of variables and a baseline comparison of both groups. For the primary outcome analysis, an average score comparison of hypothetical scenario questionnaires between the EDUCAGUIA intervention group and the control group will be performed at 1 and 6 months post-intervention, using 95 % confidence intervals. A linear multilevel regression will be used to adjust the model.

**Discussion:** The identification of effective teaching strategies will facilitate the incorporation of available knowledge into clinical practice that could eventually improve patient outcomes. The inclusion of information technologies as teaching tools permits greater learning autonomy and allows deeper instructor participation in the monitoring and supervision of residents. The long-term impact of this strategy is unknown; however, because it is aimed at professionals undergoing training and it addresses prevalent health problems, a small effect can be of great relevance.

**Trial registration:** ClinicalTrials.gov: NCT02210442.

**Keywords:** Health personnel/education, Professional competence, Games, Experimental, Problem solving, Practice guidelines as a topic

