### Sample size

The sample size has been calculated considering a relevant post-intervention average difference of 10 points on a 100-point evaluation questionnaire between groups and a standard deviation of 0.5 [31]. Assuming an alpha error of 0.05 and a beta error of 0.10, 84 subjects are required for each group. Because randomization is performed by clusters, the sample size has been adjusted to take into account the design effect. Thus, for an average of 30 residents per teaching unit, and an intraclass correlation coefficient (ICC) of 0.03 (literature shows an ICC of 0–0.052 for similar teaching interventions) [32], a design effect of 1.87 has been obtained. With these assumptions, and expecting a 25 % loss to follow-up after a 6-month period, the required sample size is 394 (197 per group).

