### Randomization

Allocation will be performed by clusters, and the randomizing unit will be the teaching units. The analysis unit will be the residents. Randomization will be performed by using the Epidat 4.1 software module to assign patients' treatments. The intervention "e-learning EDUCAGUIA" will be regarded as the treatment, and the routine CPG dissemination system will be used as a control variable. To obtain the same number of centers

in both the intervention and control groups, the option of balanced groups will be chosen.

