**Statistical analysis**

1. Descriptive and exploratory analysis: This analysis will include participants' baseline characteristics and outcomes, means and standard deviations (SD) for

continuous variables, and proportions for categorical variables with its corresponding 95 % confidence interval (CI). Baseline comparison between the two groups in terms of the score competence test and descriptive and prognostic factors will be performed by bi-variant statistical tests.

2. Inferential analysis: Student's *t* test with a 95 % CI will be performed to compare both groups' results in the competence test in terms of score at baseline and 1- and 6-month post-implementation of each CPG recommendation.
3. Multilevel analysis: a mixed model will be constructed for the evaluation of the influence of the teaching unit on the effectiveness of the intervention. The dependent variable will be the score obtained in the competence test. The model will consist of two levels: resident doctors will comprise the first level and the teaching unit will comprise the second.
4. Dropouts and missing data

Because this trial will use an online system to allocate participants and collect baseline and outcome data, participants can leave the study at any time. To minimize the possibility of dropouts and missing data, several strategies will be considered. If a participant leaves the study before randomization, the participant will be excluded and we will not consider this as missing participant data.

All statistical tests will be performed with an intention-to-treat analysis. The last observation carried forward will be used for missing data imputation, and there will be report analyses with and without imputation [36].

Significance will be set at  $p < .05$ . Calculations will be performed using MLwiN and STATA v.12 software with specific related modules.

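### The stated inferential comparison is a resident-level t test that ignores cluster randomisation, and nothing makes the planned mixed model's arm effect the primary test

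*Protocol*

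**What the plan says.** The Randomization section of the Protocol fixes the design: "Allocation will be performed by clusters, and the randomizing unit will be the teaching units". The same section then says "The analysis unit will be the residents", and chooses balanced groups so that each arm has as many centers as the other.

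The Sample size section takes the clustering into account: "Because randomization is performed by clusters, the sample size has been adjusted to take into account the design effect". It uses 30 residents per unit and an ICC of 0.03, from a cited range of 0 to 0.052, which gives a design effect of 1.87.

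The Statistical analysis section lists two analyses of the competence score:

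- Item 2, the inferential analysis: "Student's *t* test with a 95 % CI will be performed to compare both groups' results in the competence test". It applies at baseline, 1 month and 6 months, and no allowance for clustering is stated.
- Item 3, the multilevel analysis: "a mixed model will be constructed for the evaluation of the influence of the teaching unit on the effectiveness of the intervention". The score is the dependent variable, with residents at level one and teaching units at level two.

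The Abstract has the same two parts. It says "For the primary outcome analysis, an average score comparison of hypothetical scenario questionnaires between the EDUCAGUIA intervention group and the control group will be performed", using 95% confidence intervals, and then "A linear multilevel regression will be used to adjust the model". The Variables section makes the 1-month score the primary outcome and the 6-month score secondary.

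**The concern.** A two-sample t test on residents treats every resident as an independent observation. Residents of one teaching unit share an arm and, by the plan's own ICC, resemble each other. The variance of the difference between arms is therefore larger than the t test assumes by the factor of the design effect. The standard error is too small, the p-value too small and the interval too narrow.

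The plan is thus inconsistent with itself: it enrols for a design effect of 1.87 and then names, as its inferential comparison, a test that assumes a design effect of 1. The mixed model could repair this, but it is given a different purpose. Two analyses of one outcome stand side by side with no rule for which one decides. The one labelled inferential is not valid for the design. At stake is the claim of effectiveness at 1 month, judged at p < .05.

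**Working it through.** **Inputs, all from the Sample size section:** alpha 0.05 (taken as two-sided), beta 0.10, 30 residents per unit, ICC 0.03 (cited range 0 to 0.052), 25% loss over 6 months, 84 per group before inflation and 197 after.

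**1. The plan's own figures reproduce.**
- With a standardised difference of 0.5: n = 2 × ((1.96 + 1.2816)/0.5)² = 84.06 per group, stated as 84. This supports the two-sided reading.
- Design effect: DE = 1 + (30 − 1) × 0.03 = 1.87.
- 84 × 1.87 = 157.08, and 157.08 × 1.25 = 196.35, rounded up to 197 per group, 394 in all.

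**2. False-positive rate of the resident-level t test.** The true standard error is √DE times the one the test uses, so in large samples the two-sided error is 2 × (1 − Φ(1.96/√DE)), with DE = 1 + (m − 1) × ICC for m residents analysed per unit. The 25% loss gives m = 30 × 0.75 = 22.5.

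| m | ICC | DE | √DE | 1.96/√DE | Error |
|---|---|---|---|---|---|
| 30 | 0 | 1.000 | 1.00 | 1.96 | 5.0% |
| 30 | 0.03 | 1.870 | 1.37 | 1.43 | 15.2% |
| 30 | 0.052 | 2.508 | 1.58 | 1.24 | 21.6% |
| 22.5 | 0 | 1.000 | 1.00 | 1.96 | 5.0% |
| 22.5 | 0.03 | 1.645 | 1.28 | 1.53 | 12.65% |
| 22.5 | 0.052 | 2.118 | 1.46 | 1.35 | 17.8% |

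**3. Coverage.** At ICC 0.03 the nominal 95% interval covers 100 − 15.2 = 84.8% at m = 30 and 100 − 12.65 = 87.35% at m = 22.5. The standard error should be 1.37 or 1.28 times as large, respectively.

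**4. Simulation.** 20,000 null trials per setting, equal unit sizes. The Protocol gives no number of units; 197/30 = 6.6, so 7 per arm is assumed.

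| Units per arm | m | ICC | t test on residents | t test on unit means |
|---|---|---|---|---|
| 7 | 30 | 0.03 | 15.1% | 4.8% |
| 7 | 23 | 0.03 | 12.9% | 4.9% |
| 7 | 30 | 0.052 | 22.1% | 5.1% |
| 5 | 30 | 0.03 | 14.9% | 4.8% |

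The simulation agrees with the formula, and the inflation hardly depends on the number of units. A test at unit level holds its 5%.

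**5. Degrees of freedom.** With 7 units per arm, a unit-level comparison has 14 − 2 = 12 degrees of freedom. The two-sided 5% critical value is then 2.18, not 1.96.

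**The case against.** The strongest reply is that clustering is already handled. Several parts of the Protocol point that way:

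- In the Abstract, the multilevel regression sentence directly follows the description of the primary comparison, so it can be read as adjusting that comparison.
- Item 3 has the competence score as its outcome and the correct two levels. Each unit receives only one arm, so such a model can speak to effectiveness only through an arm term.
- The Discussion promises adjustment for the training variables of units and residents, which a t test cannot do.
- One of the two named programs is a multilevel package.

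A crude comparison followed by an adjusted model is also a common layout.

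Much of this stands. A reader might infer from item 2 that the effectiveness claim and its interval will rest on the t test alone, or that the trial disregards clustering. The documents do not support either reading, because a two-level model is planned and no section says which analysis decides. Nor may 13–15% be read as the trial's actual error rate. It holds only if the t test decides, at ICC 0.03 and with 22.5 to 30 residents analysed per unit. The lower figure uses a loss given for 6 months; none is given for the 1-month primary time point.

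What does not stand is that the problem is a detail for a later SAP. The exact random-effects specification could be left there, but item 2 names a test for the group comparison, and for this design that test is wrong.

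**Conclusion.** The point holds as a defect in what is written. The named inferential comparison ignores the unit of randomisation and contradicts the sample-size assumptions, and the analysis that would be valid is not made decisive.

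If the t test decides, an ineffective intervention would be declared effective about 15% of the time at the plan's ICC with 30 residents per unit, three times the stated 5%. With 22.5 per unit the rate is about 13%. Only at an ICC of zero is the test correct; at the upper cited ICC the rate reaches about 22%. If the mixed model's arm effect decides, this inflation does not arise, apart from the small-sample issue. The text leaves that choice open until results are known.

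The figures assume a two-sided test and equal unit sizes. The closed-form rates do not depend on the number of units; the advice on degrees of freedom does.

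**What to change.** In item 2 or item 3, and in the Abstract, state that the primary comparison at 1 month, and likewise the comparison at 6 months, is the arm coefficient with its 95% CI from the item 3 mixed model, with arm as a fixed effect and a random intercept for teaching unit. A t test on unit means would serve equally well.

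Because the units are probably few (about 7 per arm, an assumption), refer the coefficient to a t distribution with small-sample degrees of freedom, such as Kenward-Roger, Satterthwaite or the number of units minus 2. Scale this to the units actually recruited.

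Keep the resident-level t test only as a labelled crude description that does not decide effectiveness.

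The cost is wording only: no new data, and the named software suffices. The interval widens by 1.37 at design effect 1.87 through the standard error. With 12 degrees of freedom it widens by about 1.37 × 2.18/1.96 = 1.52 in all.

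### Item 3 of the analysis asks the two-level model how the teaching unit influences effectiveness, which a model of scores from units randomised whole cannot answer

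*Protocol*

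**What the plan says.** Statistical analysis, item 3 (Multilevel analysis), gives the model its purpose: "a mixed model will be constructed for the evaluation of the influence of the teaching unit on the effectiveness of the intervention". On the outcome it says "The dependent variable will be the score obtained in the competence test", and on the structure that "resident doctors will comprise the first level and the teaching unit will comprise the second". It mentions no arm-by-unit term, no arm-specific variance and no level for measurement occasion.

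The Randomization section says "Allocation will be performed by clusters, and the randomizing unit will be the teaching units", with equal numbers of units per arm ("the option of balanced groups will be chosen").

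The Abstract describes the same kind of model after the primary comparison of average scores: "A linear multilevel regression will be used to adjust the model". Item 2 of the Statistical analysis makes the comparison between arms by Student's t test. Item 3 does not say that the mixed model will estimate the arm effect.

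The Sample size section assumes an ICC of 0.03 and cites a range of 0 to 0.052. The Discussion expects considerable variability between units in guideline training and says it will be handled by adjusting for training variables of units and residents.

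**The concern.** Whether the unit influences effectiveness is a question about variation in the arm effect from unit to unit. Its null is that the effect is the same in every unit. To see such variation directly, one needs both arms within units. Here every unit is wholly in one arm.

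What the stated model offers is a between-unit variance, or equivalently an ICC. Its null is different: that units in the same arm do not differ in mean score. The protocol already expects that null to be false, since it inflates the sample size for an ICC of 0.03.

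An analyst who takes item 3 at its word could report ordinary clustering as evidence that the games work better in some units than others. A small unit variance could equally be reported as a uniform effect. The design supports neither conclusion.

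**Working it through.** **1. The structure.** Write the mean score of unit j as follows.

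- Control unit: μ + u_j
- Intervention unit: μ + u_j + δ + d_j

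Here u_j is the unit's score level, δ the average effect and d_j the unit's departure from it. The question in item 3 concerns Var(d). In an intervention unit only the sum u_j + d_j is seen; in a control unit only u_j. A two-level model with one random intercept estimates a single variance that pools these, so Var(u) and Var(d) are not separated.

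A simulation confirms this (14 units of 22, 5% F test of the unit variance within arms, 20,000 runs per setting):

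- same effect in every unit, score levels differing with ICC 0.03: significant in 39% of runs;
- no differences in level, effects varying across intervention units only, same average variance: significant in 38% of runs.

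The term behaves almost identically in the two situations that item 3 would need it to tell apart.

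**2. The plan's own figures, to fix a layout.** The sample size rests on "a relevant post-intervention average difference of 10 points on a 100-point evaluation questionnaire between groups", and then "Assuming an alpha error of 0.05 and a beta error of 0.10, 84 subjects are required for each group". It reproduces if the stated 0.5 is read as a standardised difference:

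- n = 2 × (1.960 + 1.282)² / 0.5² = 84.06
- design effect = 1 + 29 × 0.03 = 1.87
- 84 × 1.87 × 1.25 = 196.35, so 197 per group and 394 in all

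The number of units is not stated. 394 / 30 = 13.1, and equal arms make the total even, so 12 or 14. I take 14 (7 per arm). Completers per unit with 25% loss: 197 × 0.75 / 7 = 21.1, taken as 21.

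**3. Illustration.** Assume the unit variance is tested within arms at 5% by an F test, and that the effect is identical in every unit. With K units of m completers and ICC ρ:

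- MSB/MSW is distributed as λ × F(K − 2, K(m − 1)), with λ = 1 + mρ/(1 − ρ)
- probability of significance = P(F > F_crit / λ)

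For K = 14 and m = 21 the degrees of freedom are 12 and 280, and F_crit = 1.787.

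| ICC | λ | F_crit / λ | Probability significant |
|---|---|---|---|
| 0 | 1.000 | 1.787 | 5.0% |
| 0.01 | 1.212 | 1.474 | 13.3% |
| 0.03 | 1.649 | 1.083 | 37.4% |
| 0.052 | 2.152 | 0.830 | 61.9% |

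The result depends on the ICC, not on the SD or the size of δ.

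**4. Sensitivity at ICC 0.03.**

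- F test, other layouts: 12 units of 22, 35%; 14 of 28 (no loss), 49%; 14 of 30, 53%; 20 of 15, 33%.
- Likelihood-ratio test of the random intercept (50:50 mixture critical value 2.71): 14 units of 22, 35% by REML and 25% by ML; 14 of 30, 49% and 38%.

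**The case against.** The strongest reply is that item 3 is loose wording for allowing for teaching units. The Abstract places the multilevel regression next to the primary comparison as an adjustment, and a random intercept for unit is the right tool for that. This is a fair reading of intent, and it shows that the model itself is sound. It does not remove the problem: the methods section, which an analyst would follow, states a different purpose, and that purpose is the one the model cannot serve.

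Second, the protocol specifies no test of the unit variance and no rule for reading it. This stands. A reader might infer that the plan as written would declare an influence of the unit over a third of the time, or that its error rate is several times nominal. The documents do not support that. The 37% is the power of an assumed test to detect a real ICC of 0.03. It becomes an error only if the result is then read as variation in effect. At ICC 0, the lower end of the protocol's own range, the rate is 5%.

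Third, other information exists. A baseline test is planned for each guideline, so change from baseline by unit could be examined under assumptions. Arm-specific unit variances are another route. Unit training variables are collected, and the Discussion plans to adjust for them. This also stands: it would be too strong to say that the trial's data hold nothing on variation in effect. But item 3 names none of these routes, and adjusting for a covariate is not the same as an arm-by-covariate interaction.

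Fourth, exact model terms are commonly left to the SAP. That is true, but the point here is a purpose that the protocol states wrongly, not a missing detail.

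Finally, none of the listed objectives concerns variation of effect between units, and the arm-effect estimate is not shown to be harmed. That limits the weight of the point.

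**Conclusion.** The point holds as a mismatch between the stated purpose and what the model can estimate. With units nested in arms, the between-unit variance of the score mixes score level and effect, so it is not evidence on whether the unit influences effectiveness. This follows from the Randomization section and item 3 alone and needs no numerical assumption.

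The size is illustrative only. It rests on an F test at 5%, 14 units of 21 completers and the reading of a significant variance as an influence on effectiveness. None of these is in the protocol. On those assumptions the rate runs from 5% to 62% over the protocol's ICC range, with 37% at the planned value.

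It should not be inferred that the mixed model is the wrong model or that the arm effect is biased. For estimating the arm effect with clustering allowed for, the two-level model is appropriate, and item 3 never gives it that task. The correction is worth making because it is nearly free and prevents an unsupported conclusion.

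**What to change.** Reword item 3 along these lines: a two-level linear mixed model, with a fixed effect of arm and a random intercept for teaching unit, will estimate the intervention effect on the competence score allowing for clustering by unit. The unit variance and ICC will be reported as a description of clustering and will not be interpreted as an influence of the unit on effectiveness. This brings item 3 into line with the Abstract and supplies a cluster-adjusted arm effect, which the t test in item 2 does not provide.

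If modification by unit is of interest, add an interaction between arm and a unit characteristic already collected, either hours of EBM/CPG training in the past year or presence of a teaching plan that includes EBM/CPG. Report it as an estimate with a 95% CI and label it exploratory.

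Cost: one reworded item and at most one extra model term, with no new data. The trial gives up a claim about unit-specific effectiveness, and the interaction will be imprecise with about 14 units.

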### Competence assessment in both groups

An evaluation of baseline competence will be performed for each guideline prior to its presentation, and two further tests will be carried out at 1 and 6 months after the intervention. The test will evaluate the level of knowledge and decision-making in relation to ten hypothetical cases of routine clinical practice that are related to the content of each guideline; the test will yield a maximum score of 100 and will be completed within 45 min.

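### The two-level model is fitted to an unspecified score although each resident has three per guideline, so the single primary objective gets several 1-month estimates and no designated answer

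*Protocol*

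**What the plan says.** Protocol, Statistical analysis, item 3 sets up a mixed model for the competence test score and fixes its hierarchy: "The model will consist of two levels: resident doctors will comprise the first level and the teaching unit will comprise the second". It names neither a time point nor a guideline, and does not mention the baseline score as a covariate.

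The data are richer than one score per resident. The Competence assessment section states: "An evaluation of baseline competence will be performed for each guideline prior to its presentation, and two further tests will be carried out". Those follow-up tests come one month and six months later. Each resident therefore has three scores per guideline. The number of guidelines is not given. The Abstract also describes the primary outcome guideline by guideline.

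Statistical analysis, item 2 plans t tests between the arms on "results in the competence test in terms of score at baseline and 1- and 6-month post-implementation of each CPG recommendation". The Variables section makes the 1-month score primary and the 6-month score secondary, and the Discussion repeats that the main measurement is at 1 month. The significance threshold is p < .05, with no distinction between guidelines.

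The Hypothesis and the primary objective are each one statement about the teaching strategy as a whole. The Sample size section powers one comparison on one 100-point questionnaire.

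**The concern.** With residents as the lowest level, the model is complete only if each resident contributes one score per fit. The natural way to meet that condition is to fit it separately for each guideline and time, as in item 2. The 1-month endpoint then yields as many arm differences as there are guidelines, and the protocol does not say which of them, or what combination, decides the primary objective. If the guidelines disagree, success can be read either way after the results are seen. Each separate fit also ignores what the same resident's other tests say about the strategy's effect.

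The model also does not state the use of the baseline score, although it is collected in both groups.

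**Working it through.** **1. The plan's own figure.** Inputs from Sample size: "Assuming an alpha error of 0.05 and a beta error of 0.10, 84 subjects are required for each group"; "average difference of 10 points on a 100-point evaluation questionnaire between groups and a standard deviation of 0.5"; "for an average of 30 residents per teaching unit"; "an intraclass correlation coefficient (ICC) of 0.03"; "a design effect of 1.87 has been obtained"; 25% loss.

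- The printed SD works only as a standardised difference of 0.5, that is, an SD of 20 points. I use 20 below.
- n = 2(1.960 + 1.282)² / 0.5² = 84.06, against 84 stated.
- Design effect = 1 + (30 − 1) × 0.03 = 1.87.
- 84 × 1.87 × 1.25 = 196.35, so 197 per group. This matches. The calculation is for one score per resident.

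**2. Variance components.** Total variance is 20² = 400. The unit part is 0.03 × 400 = 12, leaving 388 to split between a stable resident part R and a residual. The protocol gives no figure for R; I assume 20 to 70% of the total. The unit and resident effects are taken as shared across guidelines. For m residents per unit and an average over K guidelines, the variance of a unit mean is

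V(K) = 12 + [R + (388 − R)/K] / m.

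**3. Separate fit against average over guidelines, m = 30.** V(1) = 12 + 388/30 = 24.93.

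| K (assumed) | Resident share | V(K) | SE relative to one guideline |
|---|---|---|---|
| 2 | 0.2 | 19.80 | 0.89 |
| 2 | 0.7 | 23.13 | 0.96 |
| 4 | 0.2 | 17.23 | 0.83 |
| 4 | 0.7 | 22.23 | 0.94 |

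The averaged estimate has an SE 4 to 17% smaller. Put the other way, the separate SE is 4 to 20% larger (1/0.96 to 1/0.83).

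**4. In points, after losses.** 394/30 = 13.1, so assume 7 units per arm; 30 × 0.75 = 22.5, so assume 22 completers per unit. SE = √(2V/7). Let r be the within-resident correlation, so R = (r − 0.03) × 400.

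- One guideline: V = 12 + 388/22 = 29.64, SE 2.91, 95% CI half-width 2.179 × 2.91 = 6.3 points (t, 12 df), power for 10 points 88%.
- Three guidelines (assumed), r = 0.5: V = 12 + (188 + 200/3)/22 = 23.58, SE 2.60.
- Three guidelines, r = 0.3 to 0.7: SE 2.46 to 2.73, half-width 5.4 to 5.9 points, power 96 to 92%.

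**5. Several tests at .05.** If any one guideline were allowed to carry the claim, the chance of at least one false positive is at most 1 − 0.95^K: 9.75% for K = 2 and 18.5% for K = 4. Those values are for independent tests. The same residents sit all of them, so the true figure is lower.

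**6. If scores were stacked without a resident level.** This is conditional, because the text does not plan it. Three occasions, m = 30:

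- Arm difference in change from baseline: SE ratio √(388/(388 − R)) = 1.12, 1.44 and 1.90 at resident share 0.2, 0.5 and 0.7, so too large.
- 1-month arm effect: the fitted unit variance absorbs (2/3)R/30. The ratio is √((24.93 + 1.78)/24.93) = 1.035 at share 0.2 and √((24.93 + 6.22)/24.93) = 1.12 at share 0.7, so slightly too large.
- Resident-level covariate, share 0.5: √[(388/3)/(200 + 188/3)] = 0.70, so about 30% too small. The Discussion plans adjustment for residents' training variables.
- One overall arm effect in balanced data: about right (within about 2% in simulation), because the unit variance takes up the missing resident variance.

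**The case against.** The strongest reply is that nothing is wrong with two levels. The protocol separates the 1-month and 6-month outcomes, and item 2 compares arms at each time for each guideline. On that reading each fit has one score per resident, the hierarchy is complete and the standard errors are correct. The Abstract defines the outcome per guideline, and the sample size is for one questionnaire, so a per-guideline fit matches both. How guidelines are summarised could be left to a statistical analysis plan, and the precision gain rests on assumed figures.

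Most of this stands. A reader might infer from the missing resident level that the trial's standard errors will be wrong. The document does not support that: stacking is not planned. Even under stacking the 1-month error would be small and conservative, and the large errors fall on a change-from-baseline contrast that the analysis section does not list. A reader might also infer that a third level is indispensable. It is not, since a resident's mean over guidelines in the existing model also gives one estimate.

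The reply does not supply a designated answer. The protocol fixes the model's outcome and levels, states one primary objective, and as written produces several 1-month tests with equal standing.

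**Conclusion.** The point holds as a correctable fault of specification. Fitted per guideline and time, the two-level model is valid, but it leaves the single primary objective with several 1-month estimates, each tested at p < .05, and no rule for reading them together. The loss of precision is modest: a combined estimate would have an SE about 4 to 17% smaller. This rests on an SD of 20, the stated ICC of 0.03, 30 residents per unit, 2 to 4 guidelines and a resident share of variance of 0.2 to 0.7; the last two are assumptions. The required sample size does not change. The need for a resident level is conditional on stacking scores.

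**What to change.** In Statistical analysis, item 3, state that the primary estimate is the arm difference in the 1-month score averaged over guidelines, adjusted for the baseline score. Obtain it in one of two ways:

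- use each resident's mean 1-month score over guidelines in the existing two-level model, with the mean baseline score as covariate; or
- model the scores nested within residents within teaching units, with the guideline's baseline score as covariate. This version also accommodates residents who miss the test for one guideline.

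Declare guideline-specific effects and 6-month effects secondary. If guideline-specific effects come from the joint model, include an arm-by-guideline term; without it the arm effect is forced to be equal across guidelines.

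The cost is slightly more modelling work, with no extra residents or tests. The real trade-off is that the primary result becomes an average over guidelines, so a strategy that works for one guideline and not another will show that only in the secondary results.
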